**FIGURE 1 F1:**
[figure not shown]
Flow diagram based on the Consolidated Standards of Reporting Trials guidelines (CONSORT): Neg, negative; CRF, case report form.

Before LHMBT, all subjects are supposed to refrain from antibiotic use and discontinue probiotics, laxatives, antidiarrheal and prokinetic agents for 2 weeks. To minimize basal hydrogen excretion, dietary restriction and avoidance of smoking for at least 24 h prior to the test and during the test are recommended. Furthermore, patients are required to avoid coarse grains, milk, juice, and alcohol in the evening before the test. Fasting for 8–12 h before the procedure is needed. Before the examination, subjects use 20 mL antiseptic mouthwash (0.05% chlorhexidine) to eliminate fermentation by oral bacteria. End-expiratory breath samples will be collected just before the ingestion of 10 g (15 mL) of lactulose in a 250 mL water solution. Gas samples are collected every 15 min until 90 min and tested immediately by the methane-hydrogen breathing analyzer DA6000 (Sunvou Medical Electronics Co., Ltd., Wuxi, China). A rise in hydrogen of ≥20 part per million (ppm) by 90 min with elevated or normal methane was considered positive. Patients with only methane levels ≥10 ppm are not eligible (Rezaie et al., 2017).

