### 2.4 Results

#### 2.4.1 Effectiveness outcomes

The primary outcome is a negative LHMBT. It is defined as a rise of hydrogen less than 20 ppm and methane less than 10 ppm within 90 min compared with screening tests.

The secondary outcomes include abdominal symptom relief and alterations in gut microbiota. The key secondary outcome we designed was similar to the relief of IBS global symptoms (Pimentel et al., 2011). Abdominal symptom remission is required to meet at least one of the following criteria: 1) The pain or distension scores of GSRS decrease at least 30% from baseline; 2) Hard stool (1/2 in BSF) and loose stool (6/7 in BSF) reduce more than 50% from baseline.

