### 2.5 Randomization and allocation

Participants will be randomized after baseline assessment to either berberine or rifaximin intervention with a 1:1 allocation. A laboratory staff member, not the investigator, used Statistical Package for Social Science Version 26.0 software (SPSS V.26.0) to produce 180 random numbers after setting the starting point according to the simple randomization. The patient codes were divided into two groups (A for berberine and B for rifaximin) according to the size of the number to form a random allocation table. The corresponding information of each code was assembled into the envelope seal. Thus, the principal investigator will remain blinded to the randomization process. Participants will be aware of the group to which they are allocated.

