### 2.6 Sample size

We calculated the sample size based on the primary outcome of eradication rate. Gatta and Scarpignato (2017) published a meta-analysis in which the overall eradication rate of rifaximin for SIBO patients according to per-protocol analysis was 72.9%. Therefore, the null hypothesis is postulated to be a rate of 72.9% (*P*
_
*0*
_). We proposed that the effective rate of berberine is 69.8% (*P*
_
*1*
_) (Wang et al., 2002; Chen et al., 2015). Using the non-inferiority design with unilateral *α* = 0.025 and power 1-β = 0.8, 82 participants will be enrolled in each group. However, assuming a 10% attrition rate, we will aim to recruit 90 participants per group.

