### 2.9 Statistical analysis

Patients who finish at least one postmedication evaluation after randomization and subsequent treatment constitute the study full analysis set (FAS) as well as the primary group of efficacy assessment, according to the intention to treatment (ITT) principle. Patients who meet the criteria and complete the observation before medication without other affected treatments during the trial will be included in the study per protocol set (PPS) as the secondary group of efficacy assessment. The study safety set consists of all cases who have safety evaluation data after taking at least one kind of drug. Rubin’s method of multiple imputation will be performed for missing values to restore natural variability and uncertainty. The complete and imputed datasets will be combined and analyzed (Little et al., 2012). Complete case analysis is used for fecal microbiota on the nature of the outcome.

Analysis will be conducted using SPSS V.26.0. The quantitative and qualitative variables were reported as mean ± standard deviation (SD), median ± interquartile range (IQR), and number (frequency). Univariate analysis of variance (ANOVA) will examine differences between groups for variables with continuous data. χ2 tests will examine differences between groups for categorical variables. Unadjusted ANOVA and adjusted analysis of covariance models will compare differences in scores from baseline and postintervention data within and between groups using FAS and PPS. Variable correlations will be analyzed through Spearman’s correlation analysis. Statistical significance was defined as a *p*-value less than 0.05.

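### The binary primary outcome is left to an unadjusted chi-square test; stratifying the risk difference by baseline methane status is a cheap and probably modest gain in efficiency, not the repair of an error

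*Protocol article*

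**What the plan says.** All places are in the protocol article.

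- **Entry (2.2 and 2.3.1).** All participants are hydrogen-positive. Section 2.3.1 says that a hydrogen rise of at least 20 ppm "by 90 min with elevated or normal methane was considered positive", and patients with raised methane alone are not eligible. The screening breath test measures both gases, and Table 1 schedules it for everyone.
- **Primary outcome (2.4.1).** A negative test is "a rise of hydrogen less than 20 ppm and methane less than 10 ppm" within 90 minutes, so both gases must be below threshold.
- **Randomisation (2.5).** Allocation is 1:1, produced "according to the simple randomization", with no stratification described.
- **Analysis (2.9).** For categorical outcomes, chi-square "tests will examine differences between groups for categorical variables". Adjusted models appear in the same paragraph, but as analysis of covariance for score changes.
- **Sample size (2.6).** A non-inferiority design on eradication rates with "unilateral *α* = 0.025 and power 1-β = 0.8", giving 82 per group before attrition. No margin is stated.

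**The concern.** A patient who enters with methane of 10 ppm or more has to bring both gases down to count as a success. A patient who enters with normal methane has to bring hydrogen down and stay below the methane threshold. One would expect the first group to succeed less often, and the reason lies in the protocol's own definitions, not in an outside source.

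The plan already uses baseline adjustment, but for scores and not for the outcome on which the trial is sized. Randomisation does not balance methane by design either. The conclusion will turn on where a confidence limit falls, so a narrower interval is useful. Conditioning on methane also stops a chance imbalance in that factor from moving the estimate, and doing so in advance avoids a choice between adjusted and unadjusted results after the data are seen.

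**Working it through.** **Inputs from the documents.** Rifaximin rate 72.9%, berberine rate 69.8%, one-sided α 0.025, power 0.80, 82 per group (all 2.6).

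**Inputs assumed, because the documents do not give them.** Prevalence of elevated methane at entry, π = 20–40%. Success of a = 75–80% with normal methane against b = 50–60% with elevated methane, in the pairs 80/50, 80/60 and 75/60 (gaps of 30, 20 and 15 points).

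**1. The plan's own figure.** The 82 per group cannot be reproduced, because a non-inferiority calculation needs a margin and none is stated. With n = [p₀(1−p₀) + p₁(1−p₁)](1.960 + 0.842)² / (margin − 0.031)², margins of 10, 15 and 20 points give 674, 227 and 113 per group. Solving for n = 82:

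- Variance sum: 0.729×0.271 + 0.698×0.302 = 0.4084.
- Standard error: √(0.4084/82) = 0.0706.
- Implied margin: 0.031 + 2.802×0.0706 = 0.229.

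The power figures below use this back-solved 22.9-point margin only as a yardstick. The protocol does not adopt it.

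**2. Variance removed by stratifying on methane.** With p = πb + (1−π)a, the reduction is 1 − [πb(1−b) + (1−π)a(1−a)] / [p(1−p)].

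| a / b | π = 20% | π = 30% | π = 40% |
|---|---|---|---|
| 75 / 60 | 1.8% | 2.3% | 2.5% |
| 80 / 60 | 3.5% | 4.4% | 4.8% |
| 80 / 50 | 7.5% | 9.2% | 9.9% |

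Lowest cell: p = 0.2×0.60 + 0.8×0.75 = 0.72; 1 − (0.2×0.24 + 0.8×0.1875)/(0.72×0.28) = 1 − 0.198/0.2016 = 1.8%. Highest cell: p = 0.68; 1 − (0.4×0.25 + 0.6×0.16)/(0.68×0.32) = 1 − 0.196/0.2176 = 9.9%.

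**3. Effect on power.** Power = Φ[(0.2287 − 0.031)/SE − 1.960], with SE = 0.0706×√(1 − reduction).

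| Variance reduction | SE | 95% half-width (points) | Power | Equivalent extra patients per arm |
|---|---|---|---|---|
| 0 | 0.0706 | 13.8 | 80.0% | 0 |
| 1.8% | 0.0699 | 13.7 | 80.7% | 1.5 |
| 5% | 0.0688 | 13.5 | 82.0% | 4.3 |
| 9.9% | 0.0670 | 13.1 | 83.9% | 9.0 |

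The last column is 82/(1 − reduction) − 82.

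**4. When the covariate is weak.** A simulation used 82 per arm, 5000 runs, 30% methane-positive, and a linear adjustment for methane and hydrogen rise with robust standard errors. With no prognostic value, power went from 80.1% to 79.1%. With weak prognostic value it went from 81.2% to 81.1%, and with moderate value from 80.7% to 83.9%. Simulation error is about 0.6 points. So the small asymptotic gain at the low end may not be realised at this sample size.

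**5. Chance imbalance.** The standard deviation of the between-arm difference in methane prevalence is √[2π(1−π)/82]: 6.2 points at π = 20% and 7.7 at π = 40%. The 95% range is therefore about ±12.2 to ±15.0 points. Multiplied by the success gap, the shift in the unadjusted difference runs from 0.15×12.2 = 1.8 points to 0.30×15.0 = 4.5 points. This is a component of the 13.8-point half-width, not an addition to it.

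**The case against.** The strongest reply is that nothing here is wrong. Under randomisation an unadjusted comparison of proportions is unbiased and keeps its type I error, and its confidence interval already allows for chance imbalance in methane. That stands. A reader might infer that the planned comparison is biased, or that an imbalance of a few points is a further threat on top of the interval. Neither follows.

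Second, the chi-square sentence is generic and does not name the primary outcome, and an unseen analysis plan might add covariates. That is fair, and it rules out calling covariates missing. But 2.9 does state a method for categorical outcomes and does say where adjustment is used, so the point is about a stated choice that can be improved.

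Third, a reader might call the adjustment free precision from a known prognostic factor. The documents do not support that. They give no methane prevalence and no success rate by methane status, and the gain can be nil. The structural link makes some prognostic value plausible but does not measure it. Nor do the documents supply an argument for adding baseline hydrogen rise: everyone enters at 20 ppm or more, and nothing shows that the excess predicts clearance.

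Fourth, the change is somewhat more than a line of wording. It has to be combined with the multiple imputation in 2.9 and settled while an open-label trial is recruiting. That also stands, and it argues for fixing one estimator before analysis.

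**Conclusion.** The point holds as a recommendation on efficiency. Of the methods stated, only an unadjusted chi-square fits the primary outcome, although a baseline variable tied to that outcome by definition is already recorded for every participant. Under the assumed 20–40% prevalence and 15–30-point gaps, stratification reduces variance by about 2–10%. That moves power from 80.0% to between 80.7% and 83.9%, or the equivalent of roughly 1.5 to 9 patients per arm. If methane is not prognostic, there is no gain. The power figures rest on the back-solved margin of about 22.9 points, which the protocol does not state.

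It should not be read as showing that the planned comparison is invalid, or that adjustment would rescue the non-inferiority analysis. A chi-square test of difference does not assess non-inferiority and no margin is given. Those are separate and more serious matters, and covariate adjustment repairs neither.

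**What to change.** In 2.9, name one primary estimator for the negative breath test: the Mantel-Haenszel risk difference, berberine minus rifaximin, stratified by baseline methane status (<10 / ≥10 ppm at the screening breath test), with a two-sided 95% confidence interval pooled across the imputed datasets. A risk difference keeps the analysis on the scale of the rates used in 2.6, which an odds ratio from a logistic model would not. Keep the unadjusted risk difference as a supportive result.

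State the non-inferiority margin separately; until then the lower limit has nothing to be compared with.

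The cost is slightly more analysis work, mainly pooling the stratified estimate and its variance over the imputations. No new data, visits or patients are needed. Section 4 describes recruitment as still under way at submission, so the change should be documented before any outcome comparison by arm is made.

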## 3 Discussion

The pharmacology of berberine has been extensively explored and revealed multifunctional activities, including anti-inflammatory (Wang et al., 2017), anticancer (Chen et al., 2019; Sun et al., 2019; Gong et al., 2020), antidiabetic (Gong et al., 2017), antihyperlipidemic and cardioprotective effects, based on its regulation of gut microbiota. To the best of our knowledge, the BRIEF-SIBO study is the first clinical trial assessing the eradication effects of a two-week intervention with berberine in SIBO patients. The effect of berberine will be fully verified by using rifaximin as the positive control. The findings of this study may have implications for the management of SIBO, especially increasing the awareness of both clinicians and patients who suffer from long-term abdominal discomfort and avoiding excessive examination. We also expect to promote clinical diagnosis and efficient management. Intervention patterns will refine and inform the development of future berberine medication designed for patients with SIBO.

The goal of therapy in SIBO is not only to eradicate the small intestinal microbiota but also to improve symptoms (Quigley et al., 2020). Thus, we set abdominal symptom remission as an important point of effectiveness. The secondary outcomes also include other symptom improvements from GSRS and alterations in the gut microbiome. Different microbiome spectra in SIBO patients after treatment with berberine and rifaximin may provide a potential explanation. Predictors may be considered in clinical practice to target SIBO patients most likely to benefit from the varied intervention.

## 4 Trial status

This study was prospectively registered on the Chinese Clinical Trial Registry platform under number ChiCTR2200057554 (15 March, 2022). The study is ongoing and has not completed participant recruitment at the time of submission. Recruitment is expected to be completed by July 2023.
